During the informed consent process, participants will be given the contact details of a designated study staff member and will be advised to contact the study team (by telephone or in person at the study site) if they have a health problem. Participants will be contacted by phone by a member of the study team to be reminded about the participation in the study and the follow-up visits. The study team will take contact details of each participant at the screening visit. A copy of the consent form and participant information sheet (PIS) will also be provided to the participant before concluding the screening visit.

This study aims to include healthy individuals who have no contraindications for receiving a YF vaccine. All screening procedures will be similar for all participants. Participants will be screened for eligibility by clinical examination, urine-based pregnancy test and blood tests for HIV serology. During the screening visit, a clinician will assess participants and check the inclusion and exclusion criteria and a rapid HIV test will be done according to Government of Kenya guidelines and the Ministry of Health, Uganda guidelines. This will include the implementation of pre-and post-test counseling as specified in national guidelines. Newly diagnosed HIV persons will be linked to comprehensive care according to the guidelines. Relevant demographic information at baseline will also be collected. Antibodies to YF virus at baseline will be used in analysis but will not be an exclusion criterion.

The screening visit may occur a maximum of 30 days before vaccination. Clinical assessments will be repeated if more than 30 days elapse between screening and proposed enrolment. However, screening and vaccination may occur on the same day.

Participants of the qualitative study evaluating vaccine policy stakeholder views and perceptions will be approached for a request to participate in an interview, scheduled at their convenience. Data collection will only be initiated upon signing an Informed Consent Form.

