## **2. Study Objectives**

### **2.1 Primary Objectives**

To determine the lowest dose (1000, 500 and 250 IU/dose) of YF vaccine that is non-inferior to the full standard dose as measured by seroconversion using the PRNT50 assay at 28 days post-vaccination.

Seroconversion is defined as a  $\geq 4$ -fold rise in neutralizing antibody titre between pre-immunization (Day 0) and post-immunization samples. Any patient who appears seronegative (PRNT50 value below the Limit of Quantification, 1:10) will be considered to have a baseline titre of LOQ/2, 1:5.

Noninferiority will be assessed by comparing the lower dose to the full dose of vaccine. Since baseline antibody levels can modulate response to the vaccine, the primary analysis will be based on the per-protocol (PP) population, which must be seronegative to YF at baseline. Secondary analysis of seroconversion at Day 28 will be performed in the intent-to-treat (ITT) population, regardless of baseline YF seropositive, and for the subset of adults which are seropositive to YF at baseline. The primary analysis time point will be when each participant has provided a Day 28 post-vaccination blood sample or has surpassed the window (+/- 3 days) to provide this sample.

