### 3.5 Definition of Analysis Populations

The per-protocol (PP) population will include randomized participants who have a blood sample at baseline and 28 days (+/- 3 days) post-vaccination, who are seronegative (PRNT50 <1:10) to YF at baseline and for whom the eligibility criteria were correctly applied. The intention-to-treat (ITT) population will comprise all randomized participants who received a dose of a study vaccine and that have at least one post-vaccination blood sample. We will also assess immunogenicity endpoints for the subset of the ITT population which has a pre-existing YF neutralizing antibodies (PRNT50 ≥1:10) at baseline (ITT YF+). As above, the same definitions will be applied to the sub-population to generate, Children ITT and Children ITT YF+ populations. The same noninferiority and safety endpoints assessed for the PP and ITT populations will be analyzed for cohort (B).

The safety (SAF) population will include all participants who received a study vaccine.

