#### **4.1.2 Secondary non-inferiority outcomes**

Geometric mean PRNT50 titre (GMT) on Day 0 and Day 28 will be calculated in the PP population. A test of non-inferiority will be performed for the difference in  $\log_{10}$  GMT from baseline to Day 28 between full-dose and lower dose. Geometric fold increase in PRNT50 titre (GMFI) between Day 0 and Day 28 in the PP population will also be calculated and a similar test of non-inferiority performed. Again, any PRNT50 value reported as below the Limit of Quantification (LOQ) will be converted to a titre of 1:5.

The above non-inferiority assessments of seroconversion, GMT and GMFI at Day 28 will also be assessed in the ITT population, in the subset of the ITT population with pre-existing YF neutralizing antibodies at baseline (ITT FV+), and in the subset of the PP population with no reported history of flavivirus infection (PP FV-).

Lower vaccine doses may change the kinetics of antibody response. The assessment of seroconversion rates, GMT, and GMFI 10 days after vaccination in the ITT population will provide important information in the context of fractional dosing in outbreak response. The three immunogenicity outcomes will also be assessed in 2 years post-vaccination in the ITT population to confirm a lasting effect of full and lower dose vaccination.

Each of the above primary and secondary immunogenicity analyses will be performed in the primary study cohort (A) and replicated in the Children (B) cohort, should the sub-studies proceed.

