#### *Secondary Non-Inferiority Analysis*

Secondary analyses will include assessment of seroconversion in the ITT population as a whole, on the subset of the ITT population with baseline seropositivity to YF, and in the subset of the PP population with no reported history of flavivirus infection. Geometric mean PRNT50 titre (GMT) and GMT fold increase (GMFI) and corresponding 95% confidence intervals (CI) on day 0 and 28 will be calculated. Non-inferiority will be calculated by the difference in GMT and GMFI between the full dose and each lower dose group. Titres will be graphically represented by reverse cumulative distributions obtained by plotting, for each possible value of the titre (abscissa), the proportion of subjects with a titre greater than this value.

Lower vaccine doses may change the kinetics of antibody response. The assessment of seroconversion rates, GMT, and GMFI 10 days after vaccination in the ITT population will provide important information in the context of low dose vaccine usage in outbreak response. These three immunogenicity outcomes will also be assessed at 1 year and 2 years post-vaccination in the ITT population to confirm a lasting effect of full and low dose vaccination.

Relationships between seroconversion and vaccine immunogenicity (PRNT50 GMT and GMFI) will be related to frequencies of specific T and B cell subsets measured by flow cytometry, chemokine and cytokine levels in sera and neutralising antibody levels to other flaviviruses. Correlations between vaccine viraemia and immunogenicity will be assessed across the different vaccine dose strata. Comparisons of immune and viraemia kinetics will be made between the adult and children trial participants using non-parametric tests, whilst accounting for the administered vaccine dose.

Adverse events occurring during the study follow up period will be analyzed and compared between groups. This will be a descriptive analysis and will include all AEs up to 28 days post-vaccination, and SAEs that occurred any time during study follow-up.

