## 6.2 Immunogenicity Analysis

### Seroconversion

|            |                                                                                                                                                                             |
|------------|-----------------------------------------------------------------------------------------------------------------------------------------------------------------------------|
| Table 2.1  | Non-inferiority of seroconversion rate in each lower dose vs. full dose of YF vaccine at Day 28 (Primary outcome) in adult PP population                                    |
| Table 2.2  | Non-inferiority of seroconversion rate in in each lower dose vs. full dose of YF vaccine at Day 28 in adult ITT population                                                  |
| Table 2.3  | Non-inferiority of seroconversion rate in each lower vs. full dose of YF vaccine at Day 28 in adult ITT population with baseline sero-positivity to YF.                     |
| Table 2.4  | Non-inferiority of seroconversion rate in each of each lower vs. full dose of YF vaccine at Day 28 in adult PP population with no reported history of flavivirus infection. |
| Table 2.5  | Non-inferiority of seroconversion rate in each lower vs. full dose of YF vaccine at Day 10 in adult ITT population.                                                         |
| Table 2.6  | Non-inferiority of seroconversion rate with each lower vs. full dose of YF vaccine at Day 365 in adult ITT population.                                                      |
| Table 2.7  | Non-inferiority of seroconversion rate with each lower vs. full dose of YF vaccine at 2 years follow up in adult ITT population.                                            |
| Table 2.8  | Non-inferiority of seroconversion rate in each lower vs. full dose of YF vaccine at Day 28 in Children PP population                                                        |
| Table 2.9  | Non-inferiority of seroconversion rate in each lower vs. full dose of YF vaccine at Day 28 in Children ITT population                                                       |
| Table 2.10 | Non-inferiority of seroconversion rate in each lower vs. full dose of YF vaccine at Day 28 in Children ITT population with baseline seropositivity to YF                    |

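### Day 10, 1-year and 2-year immunogenicity is compared only in ITT, which pools baseline YF seropositives and tilts these comparisons toward non-inferiority; a seronegative analysis is missing at these visits

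*Supplement*

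**What the plan says.** Protocol v1.6, section 8.2.1, admits people with prior YF antibody: "Antibodies to YF virus at baseline will be used in analysis but will not be an exclusion criterion". SAP 3.5 defines ITT as "all randomized participants who received a dose of a study vaccine and that have at least one post-vaccination blood sample", with no condition on baseline serostatus. The per-protocol (PP) set requires a baseline PRNT50 below 1:10 and a Day 28 sample.

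For the Day 28 primary, SAP 2.1 gives its reason for the seronegative set: "Since baseline antibody levels can modulate response to the vaccine, the primary analysis will be based on the per-protocol (PP) population". The sample-size text (SAP 3.2) counts baseline seropositives among participants who cannot be evaluated. Seroconversion is at least a fourfold change, stated as a "fold rise in neutralizing antibody titre between pre-immunization (Day 0) and post-immunization samples", with no separate rule for people who start seropositive.

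At Day 28 the SAP plans four sets: PP, ITT, the seropositive part of ITT, and PP without reported flavivirus history. At the other visits it plans one. Day 10 is in ITT (SAP 4.1.2 and 5.3.2): "The assessment of seroconversion rates, GMT, and GMFI 10 days after vaccination in the ITT population will provide important information". For the later visits SAP 5.3.2 says: "These three immunogenicity outcomes will also be assessed at 1 year and 2 years post-vaccination in the ITT population". The table list agrees. Table 2.5, for example, is "Non-inferiority of seroconversion rate in each lower vs. full dose of YF vaccine at Day 10 in adult ITT population". The tables concerned are:

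- Adults (Day 10, Day 365, 2 years): 2.5–2.7, 2.18–2.20, 2.31–2.33.
- Children (Day 10, Day 365): 2.12–2.13, 2.25–2.26, 2.38–2.39.

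All fifteen are ITT, and their titles call them non-inferiority comparisons.

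**The concern.** The reason given for a seronegative primary set is not specific to Day 28. Prior antibody can alter the response at Day 10, 1 year and 2 years as well, but the plan has no seronegative analysis at any of those visits.

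If seropositives respond, or fail to respond, much the same whatever dose they receive, they add the same contribution to each arm and pull the arms together. In a superiority trial that would be conservative. Here it moves the result toward declaring a lower dose non-inferior. The SAP ties Day 10 to outbreak use and the late visits to lasting effect, so the error at stake is an over-reassuring statement about speed of onset or durability at a reduced dose.

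**Working it through.** **The plan's own figure.** Adult n per arm = (1.96 + 1.2816)² × 2 × 0.95 × 0.05 / 0.10² = 99.8, so 100, as stated in SAP 3.2. Adding 20% gives 120 per arm and 480 in total, also as stated.

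**Inputs from the documents.** Seroconversion 95%, one-sided alpha 2.5%, margin 10 points, 100 evaluable per arm (SAP 3.2). Day 10 response 80–100% (protocol 5.2).

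**Assumptions.**

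- Seropositive share s: 5%, 10% and 20%. For adults the 20% inflation covers losses and seropositives together, unsplit; for children 5% is stated.
- Proportion q of seropositives meeting the 4-fold rule, equal in all arms: 30%, then varied.
- The 10-point margin holds at these visits. SAP 5.3.2 states it only for the Day 28 primary.
- 100 seronegatives per arm, so ITT n = 100/(1 − s) = 105, 111 and 125.

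**Dilution.** ITT rate = (1 − s)p + sq. The term sq cancels between arms, so ITT difference = (1 − s) × seronegative difference. With seronegative rates of 95% and 85%, exactly at the margin:

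| s | ITT rates (q = 30%) | ITT difference | P(declare non-inferiority) |
|---|---|---|---|
| seronegatives only | 95% vs 85% | 10 points | 3.4% |
| 5% | 91.75% vs 82.25% | 9.5 points | 3.6% |
| 10% | 88.5% vs 79.5% | 9.0 points | 4.2% |
| 20% | 82% vs 74% | 8.0 points | 5.9% |

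The last column is exact binomial enumeration of the chance that the lower 95% Wald limit lies above −10 points. The 3.4% start exceeds the nominal 2.5% because of the Wald interval at this sample size, not because of the population. As a check without that artefact, the normal formula Φ((margin − difference)/SE − 1.96), with 120 per arm in ITT and q from 20% to 80%, takes 2.5% to 3.3–3.4%, 4.0–4.4% and 5.5–7.0% at s = 5%, 10% and 20%. The direction does not depend on q.

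**GMT.** If seropositives show no dose effect, the ITT ratio is the seronegative ratio raised to the power (1 − s). A true 0.50 becomes 0.50^0.95 = 0.52, 0.50^0.90 = 0.54 and 0.50^0.80 = 0.57.

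**Power when doses are equal.** Here dilution plays no part, since there is no difference to dilute. Power changes through the variance p(1 − p) of the mixed rate. At 95% and s = 10% (normal formula, 111 per arm):

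| q | ITT rate | Power |
|---|---|---|
| 10% | 86.5% | 59% |
| 30% | 88.5% | 65% |
| 50% | 90.5% | 72% |
| 70% | 92.5% | 81% |
| 90% | 94.5% | 90% |

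Seronegatives alone (100 per arm) give 90%. At a Day 10 response of 80%, seronegatives alone give 42% and ITT gives 39–48% over the same values of q.

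**The case against.** There is a fair case for leaving ITT in place. These analyses are supporting only (SAP 3.2). The dose for children is chosen on Day 28 results in PP and ITT (SAP 3.4). Known prior vaccination and infection are exclusions, which should keep the seropositive share down. An all-comers estimate has its own relevance for outbreak use. PP cannot simply be carried over, because it requires the Day 28 sample. At 5% seropositive the false-claim rate moves only from 3.4% to 3.6%. All of this stands. It limits the weight of the point and argues for keeping ITT, but it does not supply the missing seronegative comparison.

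Three stronger readings are tempting, and the documents do not support them.

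- *Seropositives cannot be assessed by a 4-fold rise and always count as failures.* The definition covers any baseline titre, and SAP 4.1.2 plans a Day 28 analysis "in the subset of the ITT population with pre-existing YF neutralizing antibodies at baseline". A high baseline may make the rule harder to meet. The rule has no bearing on GMT.
- *The visits cannot be compared with one another.* Day 28 is also tabulated in ITT (Tables 2.2, 2.15, 2.28), so an ITT time course exists. Only the seronegative primary lacks counterparts.
- *The comparisons lose power.* That depends on an unknown rate among seropositives, and at a Day 10 response near 80% there is no clear loss.

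The Day 28 seropositive analyses, including the logistic regression in SAP 5.3.2, do not answer the point either, since they say nothing about onset or persistence.

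**Conclusion.** The point holds as an inconsistency with a known direction. At Day 10, 1 year and 2 years the plan pools participants whom its own reasoning sets aside at Day 28. To the extent that seropositives respond independently of dose, this favours non-inferiority. The effect is modest at low seropositive shares: a 10-point deficit shrinks by 0.5 to 2 points over 5–20%, and the false-claim rate rises by 0.2 to 2.5 percentage points (3.4% to 3.6–5.9%). These sizes rest on an adult seropositive share that the documents do not give, a margin not stated for these visits, and an assumed 30% 4-fold-rise rate among seropositives. The GMT figures rest on no dose effect in seropositives, which the documents do not state. The Day 28 primary is unaffected. The change is worth making, but no main conclusion of the trial depends on it.

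**What to change.** In SAP 4.1.2, 5.3.2 and the table list, add an analysis of participants with baseline PRNT50 below 1:10 who have a sample within the window of the visit in question. Apply it at Day 10, Day 365 and Day 730 for adults and at Day 10 and Day 365 for children, for seroconversion, GMT and GMFI. Do not require the Day 28 sample for membership, so the set is defined visit by visit and is not the PP set. Name it as the main or a co-reported analysis and keep the ITT tables alongside, so that the ITT time course is preserved.

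Baseline PRNT50 is already scheduled for everyone, so no new data are needed. The cost is SAP wording, additional tables, and slightly fewer participants in the seronegative set than in ITT.

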#### *Pre-existing immunity interference*

We will perform a logistic regression to evaluate the impact of vaccine dose group and pre-existing immunity to YF on rate of seroconversion at Day 28. A logistic regression analysis will be conducted within each study cohort, with adjustment for age at randomization, site, sex, and baseline YF titre (as a continuous variable) and vaccine dose group as covariates. This analysis will be conducted in the subset of the ITT population which is seropositive to YF at baseline (ITT YF+) for each study cohort.

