### **3.2 Sample Size and Power Considerations**

This study will be powered to detect non-inferiority of each lower dose of vaccine (1000 IU, 500 IU, 250 IU) compared to the full standard vaccine dose.

For the adult study, assuming a 95% seroconversion rate, 90% power, 2.5% level of significance for a one-sided test and a non-inferiority margin of 10%, which gave a sample size of 100 per arm. The 10% non-inferiority margin was chosen in consideration of the public health consequence of a loss of protection but a potential increase in vaccine dosages in a situation where vaccine stocks are insufficient to respond to an outbreak. The sample size was increased by 20% to account for: i) losses to follow up and, ii) unevaluable participants with a positive serological response for YF virus at baseline. Thus, a total sample size of 480 will be required for the four vaccine dose groups (i.e. full dose, 1000 IU, 500 IU and 250 IU).

For the study in children, we assumed a 90% seroconversion rate (accounting for lower vaccine immunogenicity reported in children [4]), 90% power, 2.5% alpha for a one-sided test and a non-inferiority margin of 10%, which gave a sample size of 190 per arm. This was increased by 10% to account for 5% losses to follow up and 5% unevaluable participants with a positive serological response for YF virus at baseline. This gave a total sample size of 420 (i.e. 210 in the full dose group and 210 in the lower dose group).

Analyses of all other efficacy and safety endpoints are supporting only. Therefore, no significant adjustments will be made for multiple comparisons.

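### The regression on pre-existing yellow fever immunity is fitted only in baseline seropositives, so it cannot estimate the effect of having versus lacking that immunity

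*Supplement*

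**What the plan says.** The subsection Pre-existing immunity interference in SAP 5.3.2 sets out a logistic regression "to evaluate the impact of vaccine dose group and pre-existing immunity to YF on rate of seroconversion at Day 28". It is run separately in adults and children, "with adjustment for age at randomization, site, sex, and baseline YF titre (as a continuous variable) and vaccine dose group as covariates". The next sentence restricts it to baseline seropositives: "This analysis will be conducted in the subset of the ITT population which is seropositive to YF at baseline (ITT YF".

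SAP 3.5 defines that set: "We will also assess immunogenicity endpoints for the subset of the ITT population which has a pre-existing YF neutralizing antibodies", meaning a baseline PRNT50 of at least 1:10. Anyone below 1:10 is outside it.

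Two statements in SAP 3.2 bear on its size. For adults: "The sample size was increased by 20% to account for: i) losses to follow up and, ii) unevaluable participants", with no split between the two causes. For children the allowance is "5% losses to follow up and 5% unevaluable participants with a positive serological response".

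Protocol 8.2.1 states that baseline YF antibody does not exclude a participant, so both serostatus groups are enrolled.

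**The concern.** The aim names pre-existing immunity as a factor to be evaluated, but within the chosen set its presence does not vary. SAP 2.1 justifies a seronegative primary population on the ground that baseline antibody can alter the vaccine response. This regression is the only model in the plan aimed at that premise, and as written it cannot compare people with and without antibody. SAP 2.1, 4.1.2 and the secondary analyses in 5.3.2 repeat the lower-versus-full-dose comparison inside ITT, ITT seropositive and per-protocol subsets; none compares seropositives with seronegatives.

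What is at stake is interpretation. Odds ratios from a small all-seropositive set, reported under a heading about interference, could be taken as evidence for or against it.

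**Working it through.** **Planned sample sizes.** With n per arm = (z0.975 + z0.90)² × [p1(1−p1) + p2(1−p2)] / margin²:

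- Adults ("assuming a 95% seroconversion rate, 90% power, 2.5% level of significance for a one-sided test and a non-inferiority margin of 10"%): (1.960 + 1.282)² × 2 × 0.95 × 0.05 / 0.10² = 99.8, so 100. Then 100 × 1.2 = 120 per arm, 480 in all.
- Children (90% rate, otherwise the same): 10.51 × 2 × 0.90 × 0.10 / 0.10² = 189.1, so 190. Then 190 × 1.1 = 209, stated as 210 per arm, 420 in all.

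Both match the SAP. No size or power is given for the immunity regression.

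**Identifiability.** In ITT YF+ a serostatus indicator equals 1 for everyone and cannot be separated from the intercept. A serostatus-by-dose term duplicates the dose indicators. This does not depend on sample size.

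**Slopes.** Age, site, sex and baseline titre make 4. Dose adds 3 in adults (7) and 1 in children (5).

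**Size of ITT YF+.**

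- Children: 0.05 × 420 = 21, about 10 per arm.
- Adults: the whole allowance is 4 × 20 = 80 of 480 (16.7%), shared with losses to follow-up. Assumed seropositivity of 5% or 10% gives 24 or 48 (6 or 12 per arm).

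**Smaller outcome class per slope.** The documents give no seroconversion rate for seropositives, so 50% (most favourable) and 70% are assumed.

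| Set | n | Slopes | At 50% | At 70% |
|---|---|---|---|---|
| Adults, 5% | 24 | 7 | 12/7 = 1.7 | 7.2/7 = 1.0 |
| Adults, 10% | 48 | 7 | 24/7 = 3.4 | 14.4/7 = 2.1 |
| Adults, whole allowance | 80 | 7 | 40/7 = 5.7 | 24/7 = 3.4 |
| Children, 5% | 21 | 5 | 10.5/5 = 2.1 | 6.3/5 = 1.3 |

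Ten per slope at 50% would need 140 adults or 100 children.

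**Behaviour of the planned model.** It was simulated with an assumed titre SD of 1.5 log2 units, titre odds ratios of 0.7 or 0.5 per doubling, and no other effects. It failed to converge or gave extreme standard errors in about 20 to 48% of runs with 24 adults, 0 to 5% with 48, at most 0.2% with 80, and 8 to 21% with 21 children. Power for an odds ratio of 0.5 was 95 to 98% with 80 adults and 9 to 13% with 21 children. For an odds ratio of 0.7 it was at most 56% and 4%. An unadjusted dose contrast of 70% versus 50% within ITT YF+ has power of 10%, 16% or 25% with 6, 12 or 20 per arm.

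**Full ITT instead.** This is illustrative: two-sided 5%, unadjusted, before losses. Adults converting at 95% if seronegative and 80% if seropositive give power of 75%, 90% or 97% with 24, 48 or 80 seropositives. Children at 90% versus 70% with 21 seropositives give 73%.

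**Sparsity that remains.** With 24 seropositive adults converting at 70%, non-converters number 456 × 0.05 + 24 × 0.30 = 22.8 + 7.2 = 30. That is 30/7 = 4.3 per slope for main effects, and 30/10 = 3 once three interaction terms are added.

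**The case against.** A reader might infer that the planned model answers nothing. The documents do not support that. Baseline titre is a covariate, so the model estimates a gradient in degree of immunity among seropositives, as well as dose effects in that group. A titre-by-dose interaction would be identifiable there too, though the SAP does not promise one. This stands, but it answers a narrower question than the stated aim.

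A reader might also infer that separation is to be expected. The adult seropositive fraction is not stated, and failure occurred in fewer than half of the simulated runs even with 24 adults. Instability is a risk, not a forecast. Seropositivity above the planning allowance would ease sparsity but would not supply the comparator.

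The analysis has low standing. SAP 3.2 calls non-primary analyses supporting, the listed secondary objectives concern other flaviviruses, the table list in SAP 6.2 has no entry for this model, and SAP 3.4 does not name it for dose selection. Tables 2.1 and 2.8 (per-protocol, seronegative) and 2.3 and 2.10 (ITT seropositive) will show both strata, though without a formal comparison. All of this bears on severity and is accepted.

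Finally, pooling is not a complete cure. The interaction would rest on the same few seropositives per arm. The outcome is also harder to reach from a higher baseline: a seronegative set to 5 needs 20, whereas a baseline of 40 needs 160. Both points stand and shape the fix.

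**Conclusion.** The mismatch between the stated aim and the analysis set is certain from the text. The effect of having versus lacking pre-existing YF immunity, and its modification of the dose effect, cannot be estimated in ITT YF+.

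The size concern is less certain. About 21 children follows from the plan's own 5%. For adults, 80 is the ceiling within the planning allowance, and 24 to 48 rests on an assumed 5 to 10%. The events-per-slope figures rest on assumed seroconversion rates, and the simulation also on an assumed titre spread.

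It should be fixed, as a supporting analysis. A reader might infer that the trial's main conclusion is at risk; it is not, because the primary analysis uses only baseline seronegatives and does not draw on this model.

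**What to change.** Amend the subsection in SAP 5.3.2 as follows:

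- Fit the model in the full ITT population of each cohort, among those with Day 0 and Day 28 titres. Use baseline serostatus (or log10 titre with values below 1:10 set to 5) and dose group as main effects, adjusted for age, site and sex.
- Treat serostatus-by-dose as exploratory.
- Use a penalised (Firth) or exact method, because non-converters and seropositives are both few.
- State that a 4-fold rise is harder to reach from a higher baseline, so a serostatus odds ratio partly reflects the definition, and read it alongside Day 28 titres.
- Keep the ITT YF+ results descriptive by arm, as Tables 2.3 and 2.10 largely do already.

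The cost is a few sentences in the SAP. It needs no new data. If the SAP can no longer be amended, SAP 1.1 already provides for describing and justifying a deviation in the final report.
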